### Sample size

On the basis of the effect sizes of the studies by Hasson-Ohayon et al. (2007), Levitt et al. (2009) and Färdig et al. (2011) [16–18], we anticipate a medium effect size of 0.40 on the primary outcome variable (self-rated IMR scale, Mueser et al. 2004, 2005 [23, 24]). On the basis of the power analyses with three times of measurement (mixed models), equal allocation to the experimental and control groups, a power of .80, alpha at 0.05, and an effect size of .40, it will be necessary to randomize 148 clients: 74 to the experimental condition and 74 to the CAU group [50, 51].

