### Randomisation

Because IMR is a relatively long-term care programme—in our pilot study at least 8 months at one session per week—the drop-out from treatment may be relatively high. Other studies had 29 % [17], 15 % [18]; 51 % [20], and 72 % [15]. Due to the 50 % drop-out rate expected from treatment in the experimental condition (a pessimistic estimate), we have chosen to allocate more clients to the experimental condition (IMR) than to the CAU group (proportions of 3:2). We will randomise 200 clients (on the basis of a conservative calculation): 120 to the experimental condition and 80 to the CAU group.

Randomisation will be stratified by team. To ensure the right distribution of clients per team in the two groups, envelopes containing five lots per team will be used each time. For this we will use a randomisation plan from http://www.randomization.com. After completing the baseline interviews, the principal investigator will allocate participants to the experimental group or control group.

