### Statistical analysis

The analyses will be based on the intention-to-treat principle. Generalized linear mixed models will be used to investigate group difference between the experimental and control conditions [52, 53], with times of measurement nested within study participants. As well as the main effects of time and condition, we will investigate whether there is a time x condition interaction effect with respect to symptoms, health complaints, number of relapses and recovery. Because number of relapses is a count variable, the analysis will use a mixed model for the poisson or negative binomial distribution. We will also test whether the addition of a random effect for the time variable results in a better model fit in each of the analyses. For the recovery outcome, we will investigate the influence of illness management, symptoms, relapses and progress on personal goals, as well as their interaction with time. Akaike’s Information Criterion (AIC [54]) will be used for statistical model selection in these analyses.

To explore associations between illness-management outcomes and recovery outcomes, we will use structural equation modelling. To investigate the associations between improvement of symptoms, recovery and fidelity (within IMR + CAU), linear mixed models will be used, with clients nested within IMR groups. As well as a fixed effect for the trainer’s fidelity score, a random intercept at the group level will be incorporated. Before testing the first and second primary hypotheses, we will test the fourth secondary hypothesis: ‘we expect that any improvement resulting from IMR + CAU will be associated with the fidelity with which IMR is implemented.’ If fidelity has an effect, it will be included as a covariate in the subsequent analyses.

Clients will be classified as completers of the study if they have finished all three interviews. After the intention-to-treat analyses, we will perform secondary analyses to measure the effects in clients who have completed IMR.

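### The planned analysis of clients who completed IMR is open to selection bias: make a complier-average estimate, with its assumptions stated, the main secondary estimate and treat any completer contrast as exploratory

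*Protocol article*

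**What the plan says.** The Statistical analysis section of the Protocol article sets the basis for the conclusions: "The analyses will be based on the intention-to-treat principle". Later it adds that, once those analyses are done, "we will perform secondary analyses to measure the effects in clients who have completed IMR". The sentence before that one defines a different kind of completion: "Clients will be classified as completers of the study if they have finished all three interviews". The section does not say what counts as having completed IMR, whom the completers are compared with, or how selection would be handled.

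The Randomisation section puts at 50% the "drop-out rate expected from treatment in the experimental condition (a pessimistic estimate"), and cites 29%, 15%, 51% and 72% from other studies. Partly for this reason the allocation is 3:2, with "120 to the experimental condition and 80 to the CAU group". The Care as usual section places no limits on what CAU clients may receive and says that care use in the control group will be registered.

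**The concern.** Clients who stay in a weekly programme for eight months or more may well have been heading for a better course than those who leave, whatever IMR does. Randomisation balances the two arms as a whole. It does not balance the completers of one arm against all of the other, and the CAU clients who would have completed IMR cannot be identified.

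An effect reported in completers is easily read as showing that IMR works when it is received. The article's Introduction already reads earlier results in that way: it notes an effect confined to high-fidelity sites in one trial and low participation in another. Completer selection is not among the weaknesses listed under Limitations. If the intention-to-treat result were diluted by drop-out, the completer result could draw more weight than it can bear.

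**Working it through.** **Inputs.** From the Randomisation section: 120 IMR and 80 CAU; drop-out from treatment 50% (pessimistic), with 15% to 72% elsewhere, so completion share c runs from 0.85 to 0.28. From the Sample size section: effect size 0.40, power 0.80, alpha 0.05, 74 per arm. Assumed, because not given: two-sided alpha, correlation 0.5 between measurements, and the gap g.

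**Step 1, the plan's own figure.** For one measurement, n = 2 × (1.96 + 0.842)² / 0.40² = 98.1 per arm. Averaging two follow-ups gives 98.1 × (1 + 0.5)/2 = 73.6, and adjusting one follow-up for baseline gives 98.1 × (1 − 0.5²) = 73.6. Both round up to 74, so 148 is reproduced under the assumed correlation. The plan gives no figure for the completer analysis.

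**Step 2, bias of completers against CAU.** Without an IMR effect, let would-be completers change by m₁ and would-be drop-outs by m₀ on average, with g = m₁ − m₀. The CAU mean is c·m₁ + (1 − c)·m₀ and the completer mean is m₁. The difference is (1 − c) × g.

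The scale is an SD of 1. At correlation 0.5 the variance of a change score is 2 × (1 − 0.5) = 1, so the same SD serves for change. SE = √(1/80 + 1/(120c)). The false-positive rate is Φ(b/SE − 1.96) + Φ(−b/SE − 1.96), where b is the bias. For an assumed g = 0.3 SD:

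| Completion c | Bias | SE | False-positive rate |
|---|---|---|---|
| 0.85 | 0.15 × 0.3 = 0.045 | 0.149 | 6% |
| 0.71 | 0.29 × 0.3 = 0.087 | 0.156 | 9% |
| 0.50 | 0.50 × 0.3 = 0.15 | 0.171 | 14% |
| 0.28 | 0.72 × 0.3 = 0.216 | 0.206 | 18% |

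At c = 0.50, g = 0.2 gives bias 0.10 and 9%; g = 0.5 gives 0.25 and 31%. A simulation of 10,000 trials at c = 0.50 gave 14.5% for g = 0.3 and 32% for g = 0.5. With g = 0 there is no bias.

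**Step 3, complier-average estimate on all 200.** The estimate is the intention-to-treat difference divided by c. The intention-to-treat SE is √(1/80 + 1/120) = 0.144, so at a single measurement the complier SE is about 0.144/c: 0.17 at c = 0.85, 0.20 at 0.71, 0.29 at 0.50 and 0.52 at 0.28.

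- No effect, g = 0.3, c = 0.50 (simulated): mean about 0, false-positive rate 5%.
- True effect 0.40 in completers, none in drop-outs, g = 0.3 (simulated): complier estimate 0.40, completer contrast 0.55. Power of the complier test is 27%, because it is in essence the intention-to-treat test.

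**Step 4, partial attendance.** Suppose drop-outs gain e. The intention-to-treat effect is 0.5 × 0.40 + 0.5 × e, and dividing by 0.5 gives 0.40 + e. For e = 0.1, 0.2 and 0.3 the complier estimate is 0.50, 0.60 and 0.70 against a true 0.40. At e = 0.2 it is further off than the completer contrast at g = 0.3 (0.55).

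**The case against.** **The method is not stated.** The article names no comparator or estimator, and its sentence could even describe a complier analysis. A reader might infer that the plan prescribes completers against all of CAU. That is an inference, though CAU is the only other arm and a before-after reading within IMR would be weaker. Estimator details may stand in a fuller document. What remains is that the article commits to an effect in a post-randomisation subset without recognising the selection.

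**The gap is assumed.** This stands. Limitations discusses selection at recruitment, not at completion. The planned condition-by-time contrast also cancels a prognostic difference that is already present at baseline and stable, so g must be a gap in change. With baseline adjustment at correlation 0.5, a stable gap of 0.3 shrinks to 0.15. The bias is then 0.5 × 0.15 = 0.075. With the variance reduced to 74/98.1 = 0.754, SE = √(0.754 × (1/60 + 1/80)) = 0.148 and the false-positive rate is about 8%.

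**Two kinds of completion.** A reader might infer that the section confuses finishing the interviews with finishing IMR. It does not: adjacent sentences use distinct terms for distinct things. Only the definition of IMR completion is absent.

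**The complier estimate has its own weakness.** This also stands. People who leave a long programme have had part of it, and step 4 shows the cost. A reader might infer that the instrumental-variable estimate settles the question and can simply replace the completer analysis. The documents do not support that: nothing says that partial attendance is without effect or that CAU clients cannot obtain IMR.

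**Conclusion.** The concern holds as a weakness of a secondary analysis. A completers-versus-CAU contrast is exposed to selection bias of (1 − c) × g, which the intention-to-treat analysis avoids. For an assumed gap in change of 0.3 SD, this is about 0.05 SD at 85% completion, 0.15 SD at 50% and 0.22 SD at 28%. For scale, the Sample size section states that "we anticipate a medium effect size of 0.40 on the primary outcome variable", so 0.15 SD would be 0.15/0.40 = 38% of the planned effect. The actual size and direction are unknown, because the documents give no gap; 50% is itself labelled pessimistic.

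A reader might infer that a particular inflated error rate has been shown, or that the trial's main conclusion is compromised. Neither follows. The error rates depend on the assumed gap, and the intention-to-treat analysis comes first and is untouched. The change is worth making because it costs little, not because the trial fails without it.

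**What to change.** Keep intention to treat as the sole basis for conclusions, and change the secondary analysis as follows:

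- Define completion of IMR in advance by sessions or modules attended. Keep the three-interview rule as a description of follow-up only.
- Name the comparator. Label any completer contrast non-randomised and exploratory, and adjust it for baseline.
- Make a complier-average causal effect the main secondary estimate of effect among completers. Use all randomised clients, with randomisation as the instrument, and record any IMR received in CAU within the planned registration of care use.
- State its assumptions: assignment acts only through completion, IMR use in CAU is absent or accounted for, and missing outcomes of drop-outs are handled explicitly.
- Add a sensitivity analysis for benefit from partial attendance, for example with sessions attended as dose or over a range of assumed effects in drop-outs. Varying the completion threshold alone does not verify the assumption.

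The cost is a few sentences, an attendance record for the IMR arm and a two-stage model. The statistical price is wider intervals (SE about 0.29 against 0.14 for intention to treat at 50% completion), no gain in power, and an overstated effect if partial attendance helps.

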#### Ethical considerations

The study protocol, information brochure and informed consent form were consistent with the declaration of Helsinki and approved by the Dutch Union of Medical-Ethic Trial Committees for mental health organisations (registration number of the Dutch National Trial Register NTR 5033 http://www.trialregister.nl, CCMO-no. NL 38605.078.12).

## Discussion

As the four RCTs conducted on IMR have yielded mixed results, more research is needed. We therefore aim to compare the effectiveness of the IMR programme with that of CAU in people with SMI. Our first primary hypothesis is that IMR + CAU will lead to better illness management and fewer symptoms and relapses than CAU only. The second primary hypothesis is that IMR + CAU will lead to better ‘subjective’ and ‘objective’ recovery than CAU only. The first secondary hypothesis is that the cost-utility of IMR + CAU will be better than that of CAU. We intend to explore the working mechanisms of IMR by testing a second secondary hypothesis that better illness management will lead to fewer symptoms and relapses. We also intend to test a third secondary hypothesis that better ‘distal outcomes’ (i.e. recovery) will result from a combination of better ‘proximal outcomes’ (i.e. better illness management and fewer symptoms and relapses) and progress on personal goals. Finally, in our fourth secondary hypothesis, we expect that any improvement resulting from IMR + CAU will be associated with the fidelity with which IMR is implemented.

Our study has various strengths and limitations.

### Strengths

The first strength is that our use of different outcome measures for each domain will provide a thorough measurement of the effects of IMR on illness management and on subjective and objective recovery. And as well as exploring the contribution made by various illness-management variables to illness outcomes, we will also explore the contribution that progress on personal goals makes to subjective and objective recovery. In this way we will be able to analyse the working mechanisms of Mueser’s conceptual framework [2].

Other strengths of our study are that it will be conducted in another country than the earlier RCTs. By including 200 participants with various types of SMI, it will also have a relatively large sample size. The numbers of participants in the other completed RCTs were 210 [17], 104 [18], 41 [16] and 118 [15]. As the study will be conducted in the everyday clinical practice of the two participating mental health institutions, the generalisability of its results will be good. The measurement procedure at the second and third time of measurement will be single blinded.

### Limitations

Firstly, no structured diagnostic interview will be used to confirm the DSM-IV diagnosis. Practical considerations underlay our choice of the clinical diagnosis reported by clinicians on the basis of the medical records; due to the limited relevance of a DSM-IV diagnosis to the present study, this seems to be sufficient.

Another limitation is the chance of recruitment bias. As we consider clinicians to be responsible for treatment, it will be they who suggest that particular clients participate in IMR, and who inform these clients about the study. Although an interview with an assistant researcher will be used to screen all clinicians’ total caseloads for their potential suitability for IMR, and although the clinicians are indeed supposed to ask all selected clients to participate in IMR and to inform them about the study, some clinicians may prefer certain clients for participation in IMR—those whose functioning is better, for example. Some of these selected clients are therefore likely to participate in this study. We will explore which criteria the clinicians use to select participants for IMR.

A further limitation is that the clinicians who score two questionnaires will not be blind for the condition. On the other hand, they will not be involved in the IMR training. Neither, due to the use of self-score questionnaires, will they be blind for the clients.

The use of multiple scales to assess aspects of objective and subjective recovery is a limitation, as multiple testing may introduce positive findings. However, given the comprehensive nature of the IMR model and training programme, we felt that it would not be enough to use IMR scales alone [23, 24], and that a more comprehensive set of scales was needed.

By limiting the cost-utility analyses to health care consumption alone, we will not be able to include potential reductions in social costs, such as those that might occur if IMR participants manage their symptoms well enough to be able to work. But a full assessment of costs is beyond the scope of this study.

Finally, IMR will be offered in our study in a group format, and will be compared with care as usual, which will largely involve an individual format. Some of the possible effect in a group format may be attributable to peer-group support.

If evidence provides support for IMR, IMR may be recommended as part of the guidelines for SMI care, and be implemented more broadly. This will enable it to meet a need for a structured psychosocial intervention that supports illness management and recovery.

## Abbreviations

AIC: Akaike’s Information Criterion
ASI: Addiction Severity Index
BSI: The Brief Symptom Inventory
CAT: cognitive adaptation training
CAU: care as usual
CNCM: The Cumulative Needs for Care Monitor
CSES: the coping self-efficacy scale
EBP: Evidence Based Practice
EQ-5D: Euro-Qol 5D
IMR: illness management and recovery
IMRS: illness management and recovery scale
IS: The Insight Scale
ISMI: The Internal Stigma of Mental Illness
IT-IS: Illness Management and Recovery Treatment Integrity Scale
MHRM: The Mental Health Recovery Measure
MSPSS: The Multidimensional Scale of Perceived Social Support
PR: Boston psychiatric rehabilitation approach
QUALYs: Quality adjusted life years
RCT: randomised clinical trial
SAMSHA: Substance Abuse and Mental Health Services Administration
SERS-SF: The Self-Esteem Rating Scale-Short Form
SES: The Service Engagement Scale
SMI: serious mental illness
U.S.: United States of America
WRAP: wellness recovery action plan
